### Secondary Outcomes:

- Asthma currently on treatment
- Death (any cause after randomisation)
- Respiratory outcomes (composite) – any respiratory diagnoses other than asthma including chronic lung disease
- Neurodevelopmental disability (composite) – any of:
  - visual impairment
  - hearing impairment
  - intellectual impairment
  - cerebral palsy
  - epilepsy
  - autism spectrum disorder (including Asperger's syndrome)
  - attention deficit disorder (ADD) or attention deficit hyperactivity disorder (ADHD)
- Cardiovascular outcomes (composite) – any cardiovascular diagnosis including hypertension, cardiomyopathies, arrhythmias, heart failure but excluding congenital heart disease
- Number of cardiovascular disease risk factors (composite categorised as 0, 1 or >1 risk factors) – any of:
  - high blood pressure
  - dyslipidaemia

- diabetes mellitus
- obesity/overweight
- Diabetes outcomes (composite) – any of prediabetes, diabetes mellitus, gestational diabetes mellitus
- Mental health outcomes (composite) – any mental health diagnosis including depression, bipolar affective disorder, schizophrenia, anxiety disorders, suicide/self-harm
- Bone health outcomes: any diagnoses related to bone disease
- Bone health outcomes: number of fractures
- General health outcomes: self-reported general health (reported health fair or poor)
- General health outcomes: functional difficulties (categorised as no disability / moderate or non-severe disabilities / severe disabilities)
- General health outcomes: oral health (reported oral health fair or poor or tooth extractions)

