| Neurodevelopmental disability (composite)

Defined as the presence of neurodevelopmental disability either of: 
 
1. Self-report of a neurodevelopmental disability.
 
2. Severe disability as classified by the Washington short set questions based on self-report questionnaire
 
3. Hospital admissions with diagnostic
 
 | Self-report questionnaire              | Responded "A lot of difficulty" or "Can't do this at all" to any Washington Short Set questions:
F6. Do you have difficulty seeing, even if wearing glasses?
F7. Do you have difficulty hearing, even if using a hearing aid?
F8. Do you have difficulty walking or climbing steps?
F9. Do you have difficulty remembering or concentrating?
F10. Do you have difficulty washing all over or dressing?
F11. Using your usual language, do you have difficulty communicating, for example, understanding or being understood? |                                           | First, we recommend a three-way disaggregation of a) persons with no difficulty in all domains; b) persons with some difficulty in one or more domains; and c) persons with a lot of difficulty in one or more domains. The three groups are mutually exclusive. They could be labelled as persons without disability, persons with moderate or non-severe disabilities, and persons with severe disabilities respectively.

https://doi.org/10.1016/j.dhjo.2023.101499 |

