| 
4. codes for a neurodevelopmental disability at any age. Whaikaha claims relating to a neurodevelopmental disability at any age
 
5. Dispensing of pharmaceuticals for ADHD or epilepsy for at least one repeat prescription more than 1 day apart and within last 2 years .
 |                                        | 
Free text response indicating a neurodevelopmental disability to one of the following questions:
 B41. Do you currently have any other major illnesses?
 B42. Have you ever had any other major illnesses in the past?
 
D1. Have you ever been told by a doctor that you have autism spectrum disorder, including Asperger's syndrome?
 
D3. Have you ever been told by a doctor that you have attention deficit disorder (ADD) or attention deficit hyperactivity disorder (ADHD disorder)?
 
Free text response in tracking database indicating a neurodevelopmental disability severe enough that the questionnaire was completed by someone other than the participant.
 |                                           |                      |
|                                                                                                                                                                                                                                                                                          | NMDS admissions data                   | Admissions with the following ICD-10AM codes:
F840 Childhood autism
F900 Disturbance of activity and attention                                                                                                                                                                                                                                                                                                                                                                                                                                                                                                                                                                                       |                                           |                      |

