| Cardiovascular outcomes (composite)

Defined as the presence of either of: 
 
1. Self-report of a cardiovascular condition.
 
2. Hospital admissions with diagnostic codes for a cardiovascular condition at any age.
 
3. Dispensing of a listed pharmaceutical for
 
 | Self-report questionnaire              | B1. Have you ever been told by a doctor that you have high blood pressure?
B5. Have you ever been told by a doctor that you have had a heart attack?
B12. Have you ever been told by a doctor that you have heart failure?
B13. Have you ever been told by a doctor that you have any other heart condition/s?

Free text response indicating a cardiovascular condition to one of the following questions: | May need to look at all of these as an adjudication committee |                                                                                                      |

| Study Outcome (definitions) | Priority Order for use of Data Sources | Details of data*:                                                                                                                                                                                                                                                                                                                                                                                                                                                                                                                                                                                                                                                                   | Criteria for adjudication (if applicable) | Comments/ Reference: |

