|                             |                                        | F60-F69: Disorders of adult personality and behaviour.
F80-F89: Pervasive and specific developmental disorders
F90-F98: Behavioural and emotional disorders with onset usually occurring in childhood and adolescence.
F99: unspecified mental disorder.
U793 Depression                                                                                                                                                                                                                                                                                                                                           |                                           |                                                                                                                                                                                                                                                                                                                                                                                                                                                                                                               |
|                             | NZ pharmaceuticals collection          | MHA medications List:
1011 Risperidone, 1030 Sertraline hydrochloride, 1069 Amoxapine, 1078 Clozapine, 1080 Amylobarbitone sodium, 1125 Nefazodone, 1140 Olanzapine, 1166 Bromazepam, 1180 Venlafaxine, 1183 Quetiapine, 1183 Quetiapine fumarate, 1193 Citalopram hydrobromide, 1315 Clomipramine hydrochloride, 1432 Disulfiram, 1437 Dothiepin hydrochloride, 1438 Doxepin hydrochloride, 1532 Flupenthixol decanoate 1533 Fluphenazine decanoate 1535 Fluphenazine hydrochloride 1642 Imipramine hydrochloride 1729 Loprazolam mesylate 1731 Lormetazepam 1732 Loxapine succinate 1760 Maprotiline hydrochloride |                                           | https://www.ncbi-nlm-nih-gov.ezproxy.auckland.ac.nz/pmc/articles/PMC7045433/

- reference for a case identification method of using the IDI for mental health research. |

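### Appendix 15.2 defines the neurodevelopmental and cardiovascular composites differently from Section 5, and its mental-health admission codes partly overlap the neurodevelopmental ones

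*SAP*

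**What the plan says.** **Neurodevelopmental composite.** Section 5 gives a closed list: visual, hearing or intellectual impairment, cerebral palsy, epilepsy, autism, and ADD/ADHD. The Appendix 15.2 row has five criteria. Criterion 2 reads "Severe disability as classified by the Washington short set questions based on self-report questionnaire", and the details column applies it to the two worst responses on any of six items. Criterion 5 reads "Dispensing of pharmaceuticals for ADHD or epilepsy for at least one repeat prescription more than 1 day apart and within last 2 years".

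**Cardiovascular composite.** Section 5 covers any cardiovascular diagnosis "but excluding congenital heart disease". Neither the outcome list that opens Appendix 15.2 nor the detailed row repeats the exclusion. The row accepts a positive answer to "B13. Have you ever been told by a doctor that you have any other heart condition/s", and adjudication is mentioned only as a possibility.

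**Mental-health composite.** Section 5 describes "any mental health diagnosis including depression, bipolar affective disorder, schizophrenia, anxiety disorders, suicide/self-harm". The admission codes in the appendix row include "F80-F89: Pervasive and specific developmental disorders" and "F90-F98: Behavioural and emotional disorders with onset usually occurring in childhood and adolescence". The neurodevelopmental row lists codes within those ranges, for example "F900 Disturbance of activity and attention".

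Neither addendum changes any of these rules.

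**The concern.** Analysts will derive the outcomes from the appendix, while readers will interpret the results from the Section 5 labels. Where the two differ, some participants count as cases without having a listed condition, some with a listed condition are missed, and some count in two composites.

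Three features of the plan make this matter. Section 3 reports that at 2 years children exposed to repeat doses more often warranted assessment for attention problems (P = 0.04), so attention is a domain of prior interest. Section 2 hypothesises no long-term harm, and cases added for reasons unrelated to treatment pull a comparison towards no difference. Section 10 makes no multiplicity adjustment and relies on reporting the number of tests, which is harder to interpret when outcomes share cases by construction.

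**Working it through.** The plan gives no figure on this point to reproduce. Its only power figure is for asthma (214 participants, 35% against 57%, 90% power). With 107 per arm assumed it reproduces at 90.3%, and nothing below depends on it. The check is mainly a comparison of texts.

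**1. Criterion 2 against the seven conditions**

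| Item | Listed condition it names |
|---|---|
| F6 seeing | visual impairment |
| F7 hearing | hearing impairment |
| F8 walking, steps | none |
| F9 remembering, concentrating | none |
| F10 washing, dressing | none |
| F11 communicating | none |

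Two of six items name a listed condition. The other four may reflect one (walking and cerebral palsy, for example), but no cause is required; a severe walking limitation after an injury would count. The severe level of the functional-difficulties outcome uses the same six items and the same threshold, so everyone at that level is also a neurodevelopmental case.

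**2. Time frames in the neurodevelopmental row**

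| Route | Time frame |
|---|---|
| D1 (autism), D3 (ADHD) | ever |
| B41, B42 free text | current or past |
| Admissions, Whaikaha claims | any age |
| Washington items | present |
| ADHD or epilepsy dispensing | last 2 years |

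Two of about 20 years is 2/20 = 10% of the dispensing history. The asthma rows show what such a window means in this plan: any asthma diagnosis uses dispensing at any age, while asthma currently on treatment uses 2 years, explained by seasonal asthma. Nothing defines the neurodevelopmental composite as current disease.

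For those whose treatment stopped more than 2 years ago:
- ADHD, questionnaire completed: D3 still identifies the diagnosis.
- ADHD, no questionnaire: only an admission or a Whaikaha record remains. Section 5 expects such participants, since it censors them at consent.
- Epilepsy, questionnaire completed: no listed question asks about it. Identification depends on free text, Whaikaha or the one epilepsy admission code, U803.

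**3. Cardiovascular row.** The admission codes are I-codes plus U822, with no congenital code. Congenital heart disease can therefore enter only by self-report, through B13 or the free-text questions.

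**4. Code match.** The neurodevelopmental row lists 18 admission codes. Those inside F80-F89 are F840, F809 and F89; inside F90-F98, F900. That is 4/18 = 22% of codes. None of the five mental-health components in the tertiary list covers them, although Section 5 says every component will be reported.

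**5. Direction of effect, with assumed values.** Let p be the risk by the intended definition and q the share of the remaining participants who become positive for an unrelated reason, equal in both arms. Observed risk = p + (1 − p)q. For placebo p = 0.20, true RR 1.5 and q = 0.05: 0.20 + 0.80 × 0.05 = 0.24; 0.30 + 0.70 × 0.05 = 0.335; RR = 0.335/0.24 = 1.40. With 107 per arm and no allowance for clustering:

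| q | RR (power), placebo 20% | RR (power), placebo 40% |
|---|---|---|
| 0 | 1.50 (39%) | 1.50 (84%) |
| 5% | 1.40 (34%) | 1.44 (80%) |
| 10% | 1.32 (29%) | 1.39 (76%) |
| 15% | 1.27 (25%) | 1.35 (71%) |

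Missed cases act differently. If the same fraction s is lost in both arms, the RR is p₁(1 − s)/[p₀(1 − s)] = p₁/p₀, so it is unchanged in expectation but rests on fewer events. It would shift if identification differed between arms, for instance through unequal questionnaire completion.

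**The case against.** Section 5 refers to the appendix for detail, so the Washington route and the 2-year window are pre-specified, and they apply equally to both arms. That answers a charge of data-driven choice. It does not reconcile a closed list with a rule that admits other conditions. The sponsor's first addendum removed the stroke question from the cardiovascular row for exactly this kind of inconsistency.

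Restricting criterion 2 also has a cost. The row has no direct question on cerebral palsy, intellectual impairment or epilepsy, so discarding four items outright could lose true cases. This stands, and it is why the fix asks for confirmation or a reasoned amendment of Section 5.

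On mental health, a reader might infer that the codes contradict Section 5, or that the two composites are not distinct. The documents do not support that. The Section 5 wording is open-ended, no rule requires composites to be exclusive, and the plan overlaps others openly (high blood pressure and diabetes each appear in two). The overlap arises only through admissions: D1, D3, Whaikaha and ADHD dispensing do not trigger the mental-health composite, and its medication list contains none of the ADHD drugs. Four of the seven F-coded neurodevelopmental entries overlap (57%), but that counts codes, not participants. The missing-component gap also applies to other listed ranges, such as F10-F19 and F60-F69.

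**Conclusion.** The mismatch holds for the neurodevelopmental and cardiovascular composites. Criterion 2 is the clearest, then the 2-year dispensing window, then the missing congenital exclusion. The mental-health overlap is a lesser point: 4 of 18 admission codes, reached by admission only.

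It would go too far to say that childhood ADHD is dropped. What is dropped is older dispensing evidence. ADHD cases are lost mainly among participants without a questionnaire who also have no admission or Whaikaha record; epilepsy losses can extend to completers. Nor is every other route lifetime, since the Washington items ask about present function.

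The effect on any estimate is unknown. The SAP gives neither rates for these outcomes nor the number of participants without a questionnaire, and the table in the working rests on assumed risks and contamination. Only secondary outcomes and their components are affected. Correction is worthwhile because the rules depart from the plan's own definitions and can be re-derived cheaply.

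**What to change.** 1. **Neurodevelopmental criterion 2:** count answers on walking, washing or dressing, remembering and communicating only when another source or blinded adjudication supports a listed condition; or amend Section 5 and give the reason. Report the composite without criterion 2 as a sensitivity analysis.
2. **Neurodevelopmental criterion 5:** count dispensing at any age and keep the repeat-dispensing requirement.
3. **Cardiovascular composite:** carry the congenital exclusion into the Appendix 15.2 outcome list and the detailed row, and screen B13 and free-text answers for it, blind to allocation.
4. **Mental-health admission codes:** remove the codes that overlap the neurodevelopmental list, or report the composite without them as well.

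The cost is edits to three appendix rows and one line of the outcome list, re-derivation from data already held, and review of the relevant self-report answers. The second addendum records that all analyses were complete before unblinding. If the groups have since been unblinded, report the corrected definitions as clearly labelled additional analyses, as Section 13 provides for post hoc work.

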## 5. Study outcomes

Outcome definitions and the hierarchical approach to different data sources are listed below and detailed in the [appendix](#). All components of the composite secondary outcomes will be reported separately as tertiary outcomes. Administrative data will be right censored at the date of the questionnaire for participants who completed the questionnaire and at the date of consent for those who did not.

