#### **Tertiary Outcomes:**

- Educational achievement outcomes: no secondary school qualification
- Educational achievement outcomes: any disciplinary action
- Social outcomes: any convictions
- Social outcomes: unemployment
- Social outcomes: alcohol use in the past year
- Social outcomes: recreational drug use
- Social outcomes: past/current smoking (pack years)
- Social outcomes: past/current vaping
- Components of neurodevelopmental disability composite outcome:
  - visual impairment
  - hearing impairment
  - intellectual impairment
  - cerebral palsy
  - epilepsy
  - autism spectrum disorder (including Asperger's syndrome)
  - attention deficit disorder (ADD) or attention deficit hyperactivity disorder (ADHD)
- Components of cardiovascular composite outcome:
  - Hypertension
  - Cardiomyopathies
  - Arrhythmias
  - heart failure
- Components of cardiovascular disease risk factors composite outcome:
  - high blood pressure
  - dyslipidaemia
  - diabetes mellitus
  - obesity/overweight
- Components of diabetes composite outcome:
  - prediabetes/diabetes mellitus
  - gestational diabetes mellitus
- Components of mental health composite outcome
  - depression
  - bipolar affective disorder
  - anxiety disorders
  - suicide/self-harm

- schizophrenia
- Components of functional difficulties outcome
  - Difficulty seeing, even if wearing glasses
  - Difficulty hearing, even if using a hearing aid
  - Difficulty walking or climbing steps
  - Difficulty remembering or concentrating
  - Difficulty washing all over or dressing
  - Difficulty communicating
- Components of obesity/overweight outcome
  - BMI
  - height
  - weight

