| Primary outcome                                                                                                                                                                                                                                                                                                                                                      |                                        |                                                                                                                                                                                                                                                                                                                                                                                                             |                                                                                                                    |                                                                                                                                                                                                                     |
| Any asthma diagnosis
Defined as the presence of either of: 
 
Self-report of a doctor's diagnosis of asthma.
 
Hospital admissions with diagnostic codes for asthma at any age.
 
Dispensing of pharmaceuticals for asthma at any age at least one repeat prescription more than 1 day apart.
 
 | Self-report questionnaire              | B22. Have you ever been told by a doctor that you have asthma?                                                                                                                                                                                                                                                                                                                                              | If answers no to question about asthma but has evidence from only one other data source, then will be adjudicated. |                                                                                                                                                                                                                     |

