| for tooth decay or gum disease                                                                                                                                                                                       |                                        |                                                                       |                                           |                      |
| Tertiary Outcomes                                                                                                                                                                                             |                                        |                                                                       |                                           |                      |
| Educational achievement outcomes: no secondary school qualification

Defined as the presence of either of:

1. Self-report of educational achievement.
2. NZQA record of highest qualification | Self-report questionnaire              | G3. What is your highest secondary school qualification?              |                                           |                      |
|                                                                                                                                                                                                                      | NZQA                                   | No record of NCEA 2 or higher                                         |                                           |                      |
| Educational achievement outcomes: any disciplinary action

Defined as the presence of MoE record of any stand-downs, suspensions, exclusions and expulsions from educational institutions               | MoE                                    | MoE record of any stand-downs, suspensions, exclusions and expulsions |                                           |                      |
| Social outcomes: any convictions                                                                                                                                                                              | MOJ convictions data                   | Data on convictions                                                   |                                           |                      |

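### The tertiary outcome 'no secondary school qualification' is an absence combined across two sources by an either-of rule, so a qualification shown in one source does not rule out a case

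*SAP*

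**What the plan says.** The outcome is listed in SAP Section 5 and again in Appendix 15.2 as "Educational achievement outcomes: no secondary school qualification". The detailed table in Appendix 15.2 gives the rule: "Defined as the presence of either of: 1. Self-report of educational achievement. 2. NZQA record of highest qualification".

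Two sources follow, in a column that gives their order of priority:
- The questionnaire comes first, with item "G3. What is your highest secondary school qualification". The answers that count as none are not stated.
- NZQA comes second. The definition calls it the "NZQA record of highest qualification", and the criterion is "No record of NCEA 2 or higher".

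The adjudication cell for this row is empty.

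Section 5 says of sources in general: "Outcome definitions and the hierarchical approach to different data sources are listed below and detailed in the" appendix. It also allows for participants who consented but did not complete the questionnaire. Section 10 sets the denominator for every outcome except death at the 214 who consented, and rules out imputation.

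**The concern.** For a disease, positive evidence in any one source is a reasonable case definition. Here the positive evidence is a qualification, and the outcome is its absence. An either-of rule then lets a gap in one source outweigh positive evidence in the other.

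The two sources also use different thresholds. The outcome name refers to having no qualification at all, whereas the NZQA criterion is met by anyone without NCEA 2 or higher. A participant who truthfully reports a lower qualification at G3 becomes a case through NZQA.

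False cases that arise equally in both arms inflate both rates and move the relative risk towards 1. The study hypothesis in Section 2 is that repeat corticosteroids have no long-term adverse effect on health and social outcomes, so dilution of this kind leans towards the expected conclusion on one of the two educational outcomes.

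**Working it through.** **Logic of the row.** The table compares three rules: the row as written; G3 deciding where it was answered; and a case only if no available source shows a qualification.

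| G3 | NZQA | Either-of | G3 decides | No source shows one |
|---|---|---|---|---|
| qualified | NCEA 2+ | not a case | not a case | not a case |
| qualified | no NCEA 2+ record | case | not a case | not a case |
| none | NCEA 2+ | case | case | not a case |
| none | no NCEA 2+ record | case | case | case |
| below NCEA 2 | no NCEA 2+ record | case | depends on the G3 threshold, not stated | depends on the threshold chosen |
| not answered | no record | case | case | case if linked, missing if not linked |

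Rows two, three and five are the problem. In the last row the SAP does not separate a participant who has no award from one who could not be found in the NZQA data. Such gaps are possible: eligibility in Section 4 rests on where the mother was randomised, and Section 3 notes that some children randomised in New Zealand were living elsewhere at 6–8 years.

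**Comparison with other rows.** For asthma the plan says "If answers no to question about asthma but has evidence from only one other data source, then will be adjudicated". For diabetes, a self-reported no is overruled by two or more other sources and adjudicated when there is only one. The education row has no equivalent.

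**Size (illustration only).** The SAP states no base rate, mismatch rate or power for this outcome, so there is no figure of its own to reproduce. Assumptions:
- True placebo rate p = 10%.
- True RR 1.63, borrowed from the asthma power calculation in Section 8 purely as a convenient value, giving 10% × 1.63 = 16.3%.
- A share m of truly qualified participants lacks the qualification in at least one source, equally in both arms.

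Observed rate under either-of = p + m(1 − p).

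- m = 5%: placebo 0.10 + 0.05 × 0.90 = 14.5%; repeat 0.163 + 0.05 × 0.837 = 20.5%; RR 1.41.
- m = 10%: placebo 0.10 + 0.10 × 0.90 = 19.0%; repeat 0.163 + 0.10 × 0.837 = 24.7%; RR 1.30. False cases are 0.09/0.19 = 47% of placebo cases. The absolute difference falls only from 6.3 to 5.7 percentage points.

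**Comparison of the three rules.** Assumptions: true placebo rate p of 10% or 20%; true RR 1.5; s = 2% of qualified participants wrongly recorded as none at G3; u = 2% to 20% of qualified participants without an NZQA record; errors independent and equal by arm. The false-case probability f is:
- either-of: 1 − (1 − u)(1 − s)
- G3 decides: s
- both sources must lack a qualification: u × s

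Observed RR = [1.5p + (1 − 1.5p)f] / [p + (1 − p)f]. False cases among 214, with the placebo rate applied throughout, = 214(1 − p)f.

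| Rule | False cases of 214 | RR (true 1.5) |
|---|---|---|
| Either-of | about 7 to 42 | 1.13 to 1.41 |
| G3 decides | about 3 to 4 | 1.42 to 1.45 |
| Both must lack it | fewer than 1 | 1.48 to 1.50 |

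For example, with p = 10% and u = 10%, either-of gives f = 1 − 0.90 × 0.98 = 0.118. The RR is then (0.15 + 0.85 × 0.118)/(0.10 + 0.90 × 0.118) = 0.250/0.206 = 1.21.

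**The case against.** The best defence is the hierarchy. Section 5 announces one, and the table puts self-report ahead of NZQA. A natural reading is that G3 decides where it was answered and NZQA otherwise. A participant who reports a qualification would then not become a case through a missing NZQA record, and dilution would be small under the assumed error rates. Section 9 also describes the outcomes as a synthesis of both sources.

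This shows that the row is ambiguous, but it does not repair it. No text makes the first source override the second, and an override would conflict with either-of. In the asthma and diabetes rows, where discordance is spelled out, a self-reported no is not final. Two analysts could derive different variables from this row.

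Three stronger inferences are not supported:
- A reader might take the row as literally reversed, since both listed items are records of achievement. The NZQA detail shows that absence is meant.
- A reader might infer that every multi-source outcome shares this wording and fault. The death row has two sources and no either-of rule. Elsewhere the phrase heads single-item lists (alcohol, drug use) and a count (fractures), so it is not used consistently as a logical operator.
- A reader might take the diluted relative risks as estimates of bias in this study. They rest on assumed inputs, and the SAP gives no rate for failed linkage or mismatch.

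**Conclusion.** The concern holds as a defect in one stated rule. Applied as written, it creates cases among participants whose qualification is shown in one of the two sources, and it applies a threshold that does not match the outcome name. The hierarchy might soften this, but the SAP does not say that it does.

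The direction of bias, towards RR 1, depends on errors being equal in the two arms. The size cannot be determined from the SAP. Severity is minor: the outcome is tertiary, and the asthma primary outcome and the power statement in Section 8 are untouched.

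**What to change.** Replace the row's definition with a rule that does the following:
1. States one threshold for both G3 and NZQA that matches the outcome name, or renames the outcome as below NCEA 2.
2. Scores a case only if no available source shows a qualification at that threshold.
3. Lets a single available source decide.
4. Treats NZQA as unavailable, not as having no record, where the participant could not be linked.
5. Sets the outcome to missing if neither source is available.
6. Sends discordant pairs to adjudication blind to treatment group.

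The last addendum states that all analyses had been completed before it was made, so this belongs in a further dated addendum that also says which rule was actually coded. The cost is that addendum, a recode and rerun of one variable, and adjudication of the discordant pairs. Section 13 plans subgroup analyses only for primary and secondary outcomes, so none need repeating. The downside is that a participant who overstates a qualification at G3 becomes a non-case unless adjudication catches it.
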